## Abstract

**Background:**

There is international recognition of the need for creative, classroom-based interventions to support children at risk of low academic achievement and well-being, due to poor attention and language skills on school entry. Working memory (WM) is a cognitive skill that is strongly associated with attention and language skills. There has been speculation that WM training, embedded within typical educational activities, may improve children’s WM skills and produce transfer effects to real-world skills such as attention and language. However, little is known about the effectiveness of this approach.

‘Recall to Enhance Children’s Attention, Language and Learning’ (RECALL) is a novel, 6-week, classroom-based intervention targeting WM, attention and language skills in 4–5 year olds. RECALL was co-produced with health professionals, teachers and parents. This protocol describes the rationale, methods and analysis plan for a proposed cluster randomised feasibility trial of this RECALL programme.

**Methods:**

This is a three-arm, cluster randomised feasibility trial comparing RECALL to an existing programme (active control), and no-intervention (education as usual). We will recruit six schools in socially disadvantaged areas in one region of the UK. Two schools will be randomly allocated to each arm of the trial. In each school, one class of children (ages 4-5 years) of approx. 30 children will be involved in this study. Ten children in each class will be sampled purposefully for outcome measurement including: standardised assessments of WM, language and attention skills; teacher ratings of attention; and parent ratings of functional communication skills. These will be administered at baseline and 1-week post-intervention in order to test the acceptability of the measures. A process evaluation using semi-structured interviews with participants will explore the acceptability of RECALL and the procedures employed in this trial.

**Discussion:**

This feasibility study will explore the acceptability of RECALL to the health professionals and teachers who will deliver it and inform the optimal design of the programme. The inclusion of an active control group and the blinding of outcomes assessors enhance rigour in this study. The findings will determine whether this study can be scaled-up into a definitive cluster randomised trial to evaluate the effectiveness of RECALL.

**Trial registration:**

ISRCTN13633886. Registered 7 Sept 2018.

## Background

Internationally, the need for classroom interventions that break cycles of academic underachievement, unemployment and poor mental and physical health is widely acknowledged [1]. In areas of low socio-economic status (LSES), high proportions of children present with impoverished language skills on school entry, and are subsequently at risk of poor school performance [2–4]. To address this, Speech and Language Therapy and other health services provide early intervention in schools through collaborative, classroom-based approaches. However, there is a lack of research-based evidence for the effectiveness of such interventions [5–7]. There is now a need for creative, therapeutic interventions to support this population [8, 9].

For children from LSES backgrounds, low language is often associated with cognitive difficulties [10, 11]. Working memory (WM) is a cognitive skill reflecting the ability to hold in mind and mentally manipulate information over short periods of time in the face of distraction [12–14]; it is strongly associated with attention skills [15–17] and language acquisition [18]. The implication of the symbiotic relationship between WM, attention and language [19] is that targeting WM as an underlying skill may produce improvements in these real-world skills [20].

Most research into the effectiveness of WM interventions has investigated computerised training packages (e.g. Cogmed 2005 [21]). The therapeutic value of this approach has been debated due to the consistently inconsistent evidence for transfer effects, i.e. the generalisation of positive effects on trained tasks to other untrained tasks [22]. In the WM literature, transfer effects have been differentiated into near-transfer and far-transfer. Near-transfer refers to improvements in untrained tasks that are similar to those trained, e.g. improvements in a visuospatial WM task following training on a verbal WM task [23, 24]. Far-transfer refers to enhanced performance in tasks quite different from those trained but which are deemed to be dependent on WM, e.g. improvement on real-world skills including language, literacy, numeracy and the ability to pay attention in class following WM training [23, 24]. The presence of near-transfer effects associated with an intervention is an essential criterion to corroborate any far-transfer effects identified [25].

On the basis that treatment effects are likely to transfer to activities with overlapping features to the trained task [26], there have been calls for WM training to be embedded within the typical activities in which benefits are needed [27, 28]. However, there has been limited research into the effectiveness of WM interventions applied with young children in everyday contexts. Furthermore, to date, the literature has focused on the cognitive benefits of WM training, and the individual differences that may moderate or mediate training and transfer effects [29, 30]. There has been little consideration of the contextual factors associated with the delivery of WM interventions in real-life settings such as schools. It has been suggested that controlling the quality, dose and fidelity of WM training in the classroom setting is challenging [29], but there has been a lack of empirical research into the barriers and facilitators of implementing WM interventions in schools.

To address this, we have developed the ‘Recall to Enhance Children’s Attention Language and Learning’ (RECALL) programme. RECALL is a theoretically underpinned, evidence-based intervention that targets WM, attention and language skills in 4–5-year-old children through group and whole-class activities over a 6-week period. It is designed to be delivered by teachers and teams of health professionals that are commissioned to reduce barriers to learning in one region of the United Kingdom (UK), Northern Ireland [31]. The Regional Integrated Support for Education (RISE) teams include speech and language therapists (SLTs), occupational therapists (OTs), physiotherapists (PTs) and social, emotional and behavioural specialists (SEBs). They support children aged between 3 and 8 years (nursery to year 4) in mainstream schools. The majority of children referred to the team are year one pupils (4–5 year olds), attending schools in areas of low socio-economic status (LSES). There is evidence that for all of the referred children, teachers have identified concerns around their attention and language skills [32]. The RISE teams have developed a whole-class programme, known as the Attention and Listening Programme (ALP), that they currently provide to schools on request. This programme is similar to RECALL in its structure and format but it is not underpinned by WM theory and has not been robustly evaluated.

This protocol describes the rationale, methods and analysis plan for a proposed cluster randomised feasibility trial that will compare RECALL to the existing ALP intervention and education as usual. It aims to resolve uncertainties about the acceptability of RECALL to those who would be delivering it (health professionals and teachers), assess the feasibility of conducting a definitive cluster randomised trial (CRT) of its effectiveness and make a novel contribution to the WM literature regarding the barriers and facilitators to the implementation of WM training in real-life contexts.

### Study aim and objectives

The key research question is whether it is possible to design a definitive CRT that will evaluate whether RECALL is more effective than an existing intervention (ALP), and education as usual, for enhancing WM, attention and language skills in 4–5 year olds from LSES areas.

We will conduct a cluster randomised feasibility trial that will enable us to:Examine the acceptability of the novel RECALL programme and its accompanying manual to the health professionals and teachers who deliver it.Measure the implementation of RECALL by health professionals and teachers including compliance and fidelity of delivery.Understand the trial processes at the cluster and individual levels including recruitment, consent and sampling procedures, attendance levels and loss to follow-up.Determine the acceptability of randomisation to schools.Explore the appropriateness of the existing intervention (ALP) as an active control comparator to the experimental RECALL programme.Explore how WM, attention and language skills are typically supported in the classroom (education as usual).Determine the appropriateness and acceptability of the outcome measures for the children, teachers and health professionals.Identify the facilitators and barriers (at the cluster and individual levels) to the implementation of RECALL and refine the intervention’s logic model.^1^

## Methods/design

This study is a three-arm, cluster randomised feasibility trial with a parallel group design. The novel RECALL classroom programme will be compared to an existing intervention (ALP, the active control) and education as usual (the no intervention control). The delivery of the interventions at the classroom level necessitates the use of a cluster design for this study [34, 35] with each school constituting a cluster. The experimental RECALL programme and the active control intervention will be delivered by health professionals from the multi-disciplinary RISE teams once per week. Thus, they will demonstrate the programmes for the teachers who will then provide two further practice sessions during the week.

Children’s outcomes will be measured at two time points (baseline and 1-week post-intervention). The protocol has been developed according to the SPIRIT 2013 Statement [36] recommendations for protocol items for clinical trials and the CONSORT 2010 extension to cluster randomised pilot and feasibility trials [37]. Throughout the trial, a process evaluation will explore the factors that could impact on the internal and external validity of a future CRT and the intervention’s logic model for RECALL will be refined [38, 39]. Figure 1 shows the flow chart of the study and Fig. 2 illustrates the timing of all trial processes.

**Fig. 1 Fig1:**
[figure not shown]
RECALL cluster randomised feasibility trial: protocol flow chart

**Fig. 2 Fig2:**
[figure not shown]
SPIRIT figure for RECALL cluster randomised feasibility trial

### Setting

This is a multi-site trial that will be conducted in primary schools in one region of the UK, Northern Ireland (NI), where children commence formal education at 4 years of age. The mainstream school population in NI includes a wide range of children including those with undiagnosed and diagnosed learning or developmental difficulties. Year one classes typically have one teacher, supported by a classroom assistant (CA). The multidisciplinary RISE teams are based within each of the five Health and Social Care Trusts (HSCT) in NI and this study will take place in two of the HSCT areas. The RISE teams work in partnership with schools and provide a range of services including: specialist assessment and intervention for referred children with recognised developmental difficulties; and targeted support for vulnerable children (considered to be at risk of developmental difficulties). Targeted interventions include whole-class and group programmes focusing on particular skills such as attention and listening. The aim of these interventions is to support all children in accessing the curriculum and reduce underachievement [40].

### Sample size and participants

As this is a feasibility study, and the purpose is to explore the acceptability of the intervention rather than its effectiveness, a formal a priori power calculation has not been conducted [41]. The results will not be used to estimate the sample size, intra-cluster correlation or treatment effects for a definitive trial because, in the case of cluster randomised feasibility trials, these can be unrealistic and misleading [42, 43]. Therefore, the number of clusters and individual participants to be recruited has been selected in order to assess the acceptability and feasibility of RECALL and the outcome measures for children’s WM, attention and language skills.

At the cluster level, six schools in areas of LSES will be recruited in total. One class of children in year one (*n = ~* 30) will participate in each school (total: *n =* ~ 180 children). Two classes will receive the RECALL programme, two will receive the active control intervention (ALP) and two will receive education as usual. In the schools allocated to the to RISE and ALP groups, all of the children in the participating classes will receive the interventions. Health professionals from the RISE teams (SLTs, OTs, PTs and SEBs) will be recruited to deliver the RECALL and active control interventions.

#### Stratification of children

At the individual level, ten children, their parents/guardians and teachers will be recruited in each class to complete the outcome measures (total sample: *n =* 60 children). Due to the age of the children involved in this study (4–5 year olds), the number of standardised measures available, particularly of WM and attention, is limited. To determine the appropriateness and acceptability of the outcome measures that have been selected, they will be trialled with children representing the typical range of ability in a year one class. Hence, we will use stratified purposeful sampling [44]. Teachers in each class will identify children in three sub-groups/strata: (1) children about whom they have concerns around listening and communication skills but do not have a diagnosed developmental or learning difficulty (*n =* 5); (2) children with diagnosed developmental or learning difficulties (*n =* 2); and (3) typically developing children who do not have any identified listening and communication problems as recognised by the teachers (*n =* 3 per class). Children considered to be typically developing, within areas of social disadvantage, will be included due to the high incidence of speech, language and communication needs in this population [3].

#### Recruitment strategy

To recruit clusters, areas of LSES will be identified using data from the Northern Ireland Multiple Deprivation Measure (NIMDM) 2017 [45]. The NIMDM ranks the super output areas in NI from the most to the least deprived across seven types (or domains) of deprivation. An initial scope of this data indicated that there are approximately 72 primary schools in LSES areas in the two HSCTs where this study will take place. These schools will be ranked according to the Education, Skills and Training domain of the NIMDM and the aim is to recruit schools within the lowest decile for each HSCT area. Two local collaborators will be consulted in order to identify schools that meet the eligibility criteria (Table 1). Schools will be contacted in writing by the researchers, followed up by a phone call and a face-to-face meeting with the principal and year one teachers to discuss the study further. If more than one teacher in a school is interested in participating in the study, one class will be randomly selected.

**Table 1 Tab1:** Cluster and individual participant eligibility criteria and rationale

Participant group	Inclusion criteria	Exclusion criteria	Rationale
Cluster eligibility (schools)	Situated in areas of LSES in the two participating HSCT areas. Have requested support from the RISE team in relation to children’s attention and language skills.	Schools with no separate year one class, i.e. all year one children are taught within a composite class with older/younger children.	RECALL was not designed for composite classes.
Education staff (teachers and classroom assistants)	Work with year one classes in a school which meets the above criteria	Previously accessed the active control (ALP) intervention.	Teachers who have previously received the active control may use strategies or activities from it in their practice which may contaminate the study findings.
Health professionals	Situated in the two participating HSCT areas. Must be SLTs, OTs, PTs or SEBs with experience in delivering whole-class programmes.	Health professionals from the teams in the three HSCT trusts involved in the co-production of RECALL.	Teams that were involved in the co-production of RECALL may be biased and this could threaten the internal validity of the study [46].
Children	Currently in a year one class, aged 4–5 years, in a school that meets the above criteria. They may have diagnosed or undiagnosed learning or developmental difficulties.	Children whose first language is not English will be excluded from being selected for outcome measurement.	The outcome measures being trialled in this feasibility study are not standardised for children whose first language is not English.

To recruit children and their parents/guardians for outcome measurement (*n =* 10 in each school), the teachers will send a user-friendly research information leaflet, participant information sheet (PIS) and consent form home with each child. Parents will return the signed consent form to their child’s teacher. From the list of children for whom consent is obtained, the teacher will choose ten pupils for outcome measurement according to the stratified sampling method. To enhance enrolment and retention in the study, parents who complete the communication skills rating scale at both the pre-and post-intervention time-points will be entered into a prize draw for a £100 supermarket shopping voucher.

To recruit the health professionals to deliver the intervention, the team mangers will identify the professionals who meet the eligibility criteria (Table 1) and disseminate the PIS and consent form. Staff will email the researcher to indicate their interest in the study and a meeting will be arranged to discuss this further and obtain written consent.

#### Eligibility criteria

Table 1 provides the inclusion and exclusion criteria for each participant group and the rationale for each prerequisite.

### Consent

At the cluster level, written consent for trial entry will be obtained from the school principals [35]. Individual consent for participation will then be obtained from all other participants [34]. The teachers, parents/guardians and children will be asked to take part without being explicitly told about which intervention they will receive. This means consent is not fully informed but it reduces the risk of selection bias and enhances the internal validity of the study [47]. The acceptability of this and its impact on recruitment will be examined in the process evaluation. Consent from the health professionals and school staff will be obtained during the pre-study meetings with the first author. Regarding children’s participation in the study, parental consent will be obtained. Child assent is deemed to be inappropriate in this study due to the age of the children. Although some 5-year-old children may be able to provide assent [48], there are considerable challenges in knowing if this is accurate [49]. The amount of autonomy children typically exercise in a given situation is also an important consideration [50]. The RECALL programme will be delivered as part of the educational curriculum and in this context children typically have limited autonomy. Although children will not assent to take part, parents will be asked to inform their children that the study is taking place and will be given a child-friendly leaflet to help them tell their child about the research. If parents do not return the consent form, the child will still receive the RECALL or active control interventions but they will not be part of the research study and no outcome measurement will be carried out with them.

### Randomisation and allocation

The six schools will be randomised to each arm of the trial: two will receive RECALL; two will receive the active control intervention (ALP); and two will receive education as usual. This will be conducted by the schools’ names being placed in opaque, sealed envelopes which will be selected by an independent person from within the lead researchers’ institute. This process has been deemed as introducing a low risk of bias in allocation concealment [51]. Randomisation will occur after baseline data collection with the children. As previously indicated, children will be selected for outcome measurement using stratification. The teacher will sort the names of all those whose parents provide written informed consent into the three strata previously specified. If more than the required number in each sub-group consent, the participants will be randomly selected using the same process of placing names in opaque envelopes.

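### The six schools are drawn without regard to the two Trust areas, so both RECALL schools may well fall in one Trust and, on the natural reading, be served by one delivery team

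*Protocol article*

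**What the plan says.** Randomisation and allocation describes a single procedure: "The six schools will be randomised to each arm of the trial: two will receive RECALL". The other four schools are shared equally between ALP and education as usual. The mechanism is "schools’ names being placed in opaque, sealed envelopes which will be selected by an independent person from within the lead researchers’ institute". Trust area plays no part in it. The only stratification in the document concerns which children in a class are measured.

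Setting states that "this study will take place in two of the HSCT areas" and that "The multidisciplinary RISE teams are based within each of the five Health and Social Care Trusts (HSCT) in NI". Under Methods/design, both programmes "will be delivered by health professionals from the multi-disciplinary RISE teams once per week", with teachers repeating the modelled session twice more each week. Sample size and participants confirms that "Health professionals from the RISE teams (SLTs, OTs, PTs and SEBs) will be recruited to deliver the RECALL and active control interventions". Table 1 requires these professionals to be "Situated in the two participating HSCT areas. Must be SLTs, OTs, PTs or SEBs with experience in delivering whole-class programmes", and excludes staff from the three Trusts that helped to co-produce RECALL.

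Recruitment strategy aims for schools in the lowest deprivation decile of each Trust area, which implies that both Trusts will contribute. It fixes no number per Trust.

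**The concern.** Several objectives concern delivery: acceptability to health professionals and teachers, compliance and fidelity, and barriers and facilitators. Only two schools receive RECALL. If both lie in the same Trust, the whole picture of RECALL in use probably comes from one Trust's team, and the other eligible team never tries it. Because Table 1 rules out three of the five Trusts, there are only two such teams.

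The comparator question is also exposed. Table 3 relies on health professionals' views of how the two programmes resemble or differ from each other, and Data analysis plans between-group ANCOVAs to inform the future model. If RECALL sits wholly in one Trust and ALP wholly in the other, every difference between them is also a difference between Trusts, and neither team may have delivered both.

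**Working it through.** **Inputs.** Six schools, three arms, two schools per arm (Randomisation and allocation): 3 × 2 = 6, which agrees with the stated total. Two Trust areas (Setting). The number of schools per Trust is not stated, so 3+3 is assumed, with 4+2 and 5+1 as the range. The protocol gives no figure of its own for balance across Trusts.

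**Number of draws.** 6!/(2! × 2! × 2!) = 90 equally likely allocations.

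**Both RECALL schools in one Trust.** With a schools in Trust A and b in Trust B, the probability is [C(a,2) + C(b,2)] / C(6,2):
- 3+3: (3 + 3)/15 = 6/15 = 36/90 = 40%
- 4+2: (6 + 1)/15 = 7/15 = 42/90 = 46.7%
- 5+1: (10 + 0)/15 = 10/15 = 60/90 = 66.7%

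**RECALL wholly in one Trust and ALP wholly in the other.**
- 3+3: RECALL falls in one Trust with probability 6/15. That leaves one school there and three in the other Trust, so ALP falls wholly in the other with probability C(3,2)/C(4,2) = 3/6. The product is 6/15 × 3/6 = 18/90 = 20%.
- 4+2: RECALL in the larger Trust and ALP in the smaller: 6/15 × 1/6 = 6/90. The reverse: 1/15 × 1 = 6/90. The sum is 12/90 = 13.3%.
- 5+1: impossible, 0%.

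**Both Trusts hosting both programmes, 3+3.** RECALL split and ALP split: 9/15 × 4/6 = 36/90 = 40%.

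| Split | RECALL in one Trust | RECALL and ALP in opposite Trusts |
|---|---|---|
| 3+3 (assumed) | 40% | 20% |
| 4+2 | 46.7% | 13.3% |
| 5+1 | 66.7% | 0% |

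A full enumeration of the 90 allocations gives the same counts.

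**What a single-Trust draw would affect.** Compliance and fidelity plans three observed RECALL sessions per school, so 2 × 3 = 6 in all, two of them led by health professionals. All six would come from one Trust.

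**After the change.** With 3+3 and one school per arm drawn in each Trust, 3! × 3! = 36 of the 90 allocations remain admissible, and both risks are 0. The zero needs the 3+3 recruitment as well as the restricted draw. With 4+2 or 5+1, some arm must lie wholly in one Trust however the draw is made.

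**The case against.** The best case for leaving the draw alone has four parts.

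- **The link from team to Trust is inferred.** The protocol says that teams are based within Trusts. It does not say that each team serves only its own schools, or that the same people would deliver in both RECALL schools. This stands. The inference is the natural one, but it is not a stated fact.
- **The consequences are limited.** Sample size and participants rules out using the results to estimate treatment effects or the intra-cluster correlation. Data analysis rules out significance testing of effects. The primary progression factor is recruitment, retention and completion of measures. This lowers the severity, but it does not touch the delivery objectives.
- **Restriction has a price.** Both Trusts would always host both programmes, against 40% of unrestricted 3+3 draws. Blinding warns that teacher blinding is harder when schools are close together, and Table 1 excludes staff with earlier ALP exposure because of contamination. A target per Trust may also be hard to meet. There are about 72 schools in disadvantaged areas; if the lowest decile means a tenth of these (an assumption), that is about seven, or three to four per Trust if evenly divided. These costs are real.
- **Two schools cannot separate team from school.** With one RECALL school per Trust, team, school and teacher coincide. This stands.

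A reader might also infer a larger risk from the chance that any arm at all lies in one Trust: 60% with 3+3 and 100% with 4+2 or 5+1. The documents do not support reading those figures as the chance that RECALL is seen with one team. Education as usual has no delivery team, and with 4+2 the chance that RECALL or ALP is affected is 66/90 = 73.3%. For what is learned about RECALL delivery, the relevant figures are 40%, 46.7% and 66.7%.

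**Conclusion.** The point holds as a weakness of the stated randomisation procedure. Under every split that uses both Trusts, the chance that both RECALL schools lie in one Trust is at least 40%. With 3+3 there is a further specific risk of 20% that RECALL versus ALP is fully confounded with Trust. These figures rest on an assumed number of schools per Trust; their meaning for delivery rests on the inference that each RISE team works in its own area.

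A reader might conclude that restricting the draw would let team problems be told apart from problems with RECALL. It would not, because there would still be one RECALL school per team. The gain is that RECALL is observed in both delivery settings. Since this is a feasibility trial that disclaims effect estimation, the change lies between worth considering and advisable, with moderate confidence.

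**What to change.** State in Recruitment strategy that the aim is three schools in each HSCT area. State in Randomisation and allocation that the draw is made within area, using two sets of three envelopes, with one school each to RECALL, ALP and education as usual. The independent person and the sealed envelopes stay as they are.

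Add a fallback. If 3+3 cannot be reached, restrict the draw so that the two RECALL schools, and where possible the two ALP schools, are in different Trusts. The fallback makes some allocations predictable: with 4+2, if both programmes are split, neither school in the smaller Trust can be drawn to education as usual; with 5+1, the single school must receive RECALL. The 3+3 target is therefore clearly preferable, and any use of the fallback should be reported.

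The cost is a sentence or two, a second set of envelopes and a recruitment target per Trust. Because both Trusts would always host both programmes, the process evaluation, which already examines teacher blinding, should also record any contact or sharing of material between RECALL and ALP schools and staff within a Trust.
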